## Abstract

**Background:**

Behavioural risk factors may often present during adolescence and account for 70% of premature deaths during adulthood. Excessive sedentary behaviour and screen time have become significant concerns, especially among adolescents, due to their potential negative impact on physical and mental health. Adolescents with a high screen-based sedentary time are more likely to be physically inactive, have unhealthy body structure and poor academic performance. The objective of our study is to assess the effect of multi-component modular educational intervention on screen-based sedentary time (SST) and non-screen-based Sedentary time (NSST) among adolescents.

**Methods:**

Ethical approval for the study has been obtained from the institutional Ethics Committee of Kasturba Medical College in Mangalore, India. This cluster randomized control trial will be carried out in schools located in the urban area of Mangalore. Using simple randomization, the eligible schools will be randomized into intervention and control arms, each consisting of 10 clusters. A multi-component modular educational intervention will be administered to participants in the intervention group at baseline, second and fourth month. The control group will receive the standard curriculum. Both the groups will be assessed at baseline and at second month, fourth month and sixth month of follow up for SST, NSST and level of physical activity. Anthropometric measurements like height, weight, waist circumference and hip circumference will be taken at baseline and sixth month of follow up.

**Results:**

A comprehensive school-based modular educational intervention can have cumulative advantages by reducing screen- and non-screen-based sedentary time, and encouraging physical activity. Similar modular teaching can be incorporated into the curriculum, which will promote healthy life-style among the adolescents.

## Introduction

Non-communicable diseases (NCDs) according to the World Health Organization (WHO) are long-lasting, non-infectious conditions with slow progression that are brought on by a confluence of genetic, physiological, environmental, and behavioral variables.
^
1
^ Around 41 million deaths, viz seventy-four per cent of total deaths worldwide each year are attributed to NCDs. This number includes 14 million premature deaths from NCDs, the bulk of which are preventable.
^
2
^ By 2030, it is anticipated that 55 million people will die annually from NCDs if immediate and appropriate interventions are not made.
^
3
^

Behavioural factors including lack of physical activity (PA) and unhealthy diet result in metabolic conditions like weight gain and obesity, high blood pressure, high cholesterol, and high blood sugar levels which are the main risk factors for NCDs. Rapid globalization and urbanization have resulted in the spread of unhealthy diets and poor lifestyles worldwide.
^
4
^ Given that these behavioural factors contribute significantly to the development of the majority of non-communicable diseases (NCDs), their effects on health across the lifespan of an individual, especially during adolescence have gained considerable attention in recent times.
^
5
^

According to the WHO, adolescents are young people, aged 10 to 19, who are rapidly developing in terms of their bodies, minds, and social connections.
^
6
^ It is also a crucial period for the establishment of health-related behaviours and lifestyle choices. Physical inactivity, substance use, unhealthy diet, being overweight and obesity are all risk factors for NCDs which are not seen as potential threats during adolescence. However, these risk factors that begin during adolescence account for 70% of premature deaths during adulthood.
^
7
^

In response to the WHO Global Action Plan for the Prevention and Control of NCDs, India developed a National Action Plan to reduce the number of premature deaths due to NCDs.
^
8
^ However, until recently the discussion around NCD prevention strategies mostly overlooked adolescents and focused only on the adult population.
^
9
^

Research involving sedentary time and sedentary behaviour has gained importance in recent times.
^
10
^ Evidence demonstrates a strong link between excessive sedentary behaviour and poor health outcomes. Sedentary behaviour as an independent entity has drawn a lot of attention as a risk factor for poor physical and mental health outcomes in children and adults.
^
11
^

**Sedentary behaviour (SB)** is any waking behaviour that involves sitting, reclining, or lying down while spending less than 1.5 metabolic equivalents of task (MET) of energy. It is seen in various domains in an adolescent’s life at home, at school, while using transport, and during free time. Examples include sitting in the school bus, playing board games, watching television, reading while sitting or lying down, and sitting in the classroom.
^
10
^ Excessive sedentary behaviour and screen time have become significant concerns, especially among adolescents, due to their potential negative impact on physical and mental health.

**Screen time (ST)** refers to the amount of time an individual spends engaged with screens, such as watching television, using computers, playing video games, or using smartphones and tablets.

**Screen-based sedentary time (SST)** is the amount of time spent using a screen-based device while being sedentary in any setting (e.g., school, home, or recreation). Examples of such devices include smartphones, tablets, computers, and televisions. SST, and in particular the time spent viewing television, is thought to be a key proxy for sedentary behaviour in adolescents.
^
11
^

Sedentary behaviour and screen time are closely related since screens often serve as the platform for various sedentary activities. The ease of accessibility and its utility for both academics and entertainment has led to a rise in screen time among children and adolescents. The recent COVID-19 pandemic led to significant changes in various aspects of our lives, including time spent using screens. Online classes and social isolation brought on by frequent lockdowns during the pandemic have also led to an increase in screen time among children and adolescents.
^
12
^ Various research studies have generated evidence indicating the relation between excessive screen time and the development of depression, anxiety, inattention, poor sleep, and physical inactivity among children and adolescents.
^
13
^

**Non-screen-based sedentary time (NSST)** is time spent engaging in sedentary activities, that don’t include the use of a screen such as doing paper-based homework, reading a physical book, playing board games and time spent on car rides and studying.
^
11
^

As per the recommendations by WHO and the American Academy of Paediatrics (AAP), children under the age of two should not spend any time seated in front of a screen (such as watching TV or videos or playing computer games), and children between the ages of two and five should restrict their screen time to no more than one hour (less is ideal).
^
14
^ Adolescents who watch TV, use computers, or play video games for more than two hours a day (screen-based sedentary time) are more likely to have an unhealthy body structure, poor fitness, and poor academic performance. Despite this, more than 30% of adolescents in the majority of countries around the world engage in screen-related behaviour that lasts more than two hours per day.
^
15
^

According to the WHO’s recommendation on sedentary behaviour, children and adolescents should limit their time spent sitting, especially screen time for leisure.
^
16
^

Over the past ten years, considerable research interest has been generated due to the rise in screen time use and its detrimental effect on health. As a result, intervention studies targeting a variety of demographic groups and contexts have been conducted to reduce screen-based sedentary time.
^
17
^
^–^
^
20
^

Interventional studies to reduce screen time targeting adolescents in schools in various Western and Latin American countries have been shown to bring about a significant reduction. The interventions applied in these studies can be categorized into three distinct groups: interventions consisting of motivational/volitional components such as health education sessions on healthy lifestyle, interventions using mass media and other health promotion materials like posters, and newsletters, and interventions involving modification of physical environments like standing desks and policy modifications such as curriculum changes.
^
21
^

This study aims to decrease screen-based and non-screen-based sedentary time in school-going teenagers through a multi-component modular educational intervention. Our study will indirectly focus on the third Sustainable Development Goal (SDG) ‘Good Health and Well-Being’ which aims to promote mental health and wellbeing while reducing premature mortality from noncommunicable diseases by one-third through prevention and early treatment.

### Hypothesis

Adolescents who receive a multi-component intervention targeting screen time and sedentary behaviours will show a significant reduction in screen sedentary time (SST) and Non screen sedentary time (NSST) compared to those who do not receive the intervention.

### Knowledge gaps

Reducing screen time among school-aged children is an important public health goal, as excessive screen time has been associated with various negative health outcomes, including obesity, sleep problems, and reduced physical activity. School-based interventions can play a critical role in addressing this issue.

However, a considerable knowledge gap still exists in this area. While some school-based interventions have shown promise in reducing screen time among students, there may be a lack of comprehensive understanding of the most effective strategies. Research is needed to identify whether the combination of interventions is successful in a school settings. There has been a limited number of school-based intervention studies for adolescents to decrease screen and non-screen-based sedentary time using a multi-component approach.

It may be regarded as an effective method to encourage adolescents to self-regulate their screen use. However, there hasn’t been much experimental research in India looking at the effects of such interventions The current study aims to close a gap in the body of knowledge on the effectiveness of a multi-component modular intervention on sedentary behaviour involving screens and other devices in urban Mangalore’s teenage populations.

### Literature review

In a school-based cross-sectional study in Brazil carried out among 2874 high school students in the age group between 14 and 19 years, the prevalence of high screen time was 79.5%. A higher proportion of males were engaged in high screen time compared to female students (84.3% vs.76.1%). On multivariate analysis, students belonging to high socio-economic status had higher odds of prolonged screen exposure. The level of physical activity and nutritional status was not found to be associated with high screen time among adolescents in the study.
^
22
^

In a cross-sectional study in Mumbai among 772 school-going adolescents in the age group between 10-15 years, screen time was high among girls compared to boys (218.21 min/d vs.165.3 min/d, p < 0.001). The combined prevalence of being overweight and obesity was 38.3%, low physical activity (PA) 38% and ST >120min/d was 85%. Clustering of high ST and low PA was seen in 69.2%. The odds of being overweight or obese in boys reporting low PA were 2.10 times higher, while the odds were 4.13 times higher in those with low PA+ST > 120 min/d. The study concluded that integrated interventions are necessary to allow greater reductions in obesity risk behaviours.
^
23
^

In a cross-sectional study in China among 971 children, it was observed that children typically spent one hour per day engaging in screen-based sedentary activity (SST) and one hour per day engaging in non-screen-based activity (NSST). Children were more likely to be overweight if they spent more time in SST. There was no connection between time spent on the NSST and overweight children (P > 0.05). This study demonstrated no link between NSST and being overweight, however, a correlation was observed between children who spent more time in SST and their likelihood of becoming overweight.
^
13
^

In a community-based cross-sectional study in New Delhi among 10 to 19-year-olds, the average daily screen time was calculated to be 3.8 hours. The majority of screen time—2.8 hours per day—is spent watching television. 68% of the teenagers admitted to watching television for more than the stipulated two hours a day.
^
24
^

In a cluster-randomised trial carried out among 8
^th^ and 9
^th^ graders of 20 urban schools in Cuenca-Ecuador, behavioural intervention was administered in two stages. Stage one of the intervention included diet, physical activity and screen time, while stage two included only diet and physical exercise. The screen time was evaluated at baseline, at 18 months for stage one and 28 months for stage two. At the end of the 18
^th^ month of follow-up, lower TV time during weekday and weekends, and lower total screen time during weekday was observed among the intervention group. However, at the end of the 28
^th^ month of follow-up, the TV time and total screen time on weekdays increased in the intervention group. The study concluded that the intervention to reduce screen time worked only if the intervention was specifically targeted at reducing screen time.
^
17
^

In an RCT carried out among 251 children aged 9 to 12 years in New Zealand, 127 children received intervention for 20 weeks which included training and educating the parent/caregiver on various strategies to reduce screen time. Screen time (TV) monitoring devices, mobility exercises, and support via online and newsletter were some of the interventions. The intervention group had more children participate in moderate-intensity physical activity (24.3 min/d; 95% CI: 0.94, 49.51; p = 0.06). No significant difference was observed in the BMI z score (−0.016; 95% CI: −0.084, 0.051; p = 0.64). The study concluded that home intervention to decrease screen time during leisure did not significantly reduce screen time or BMI.
^
18
^

A school-based cluster randomized control trial was conducted among 361 adolescents in the age group between 12-14 years in Australia which involved a 20-week intervention program. It included pedometers for self-monitoring physical activity, a smartphone app, a website, interactive seminars led by researchers, fitness equipment provided to schools, teacher-led physical education classes, lunchtime physical activity mentoring sessions, and newsletters for parents about screen time. The recreational screen time was recorded at baseline, 8
^th^ month and 18
^th^ month of intervention. Self-motivated screen time was significantly reduced by the intervention, while parental screen time guidelines were unaffected.
^
19
^

In an umbrella review that included systematic reviews and meta-analyses of interventions among children and adults directed at reducing sedentary behaviour (screen time, sitting time, or sedentary time), the interventions were found to be more successful at reducing sitting time than either physical activity alone or physical activity and sedentary behaviour combination interventions. There were slight but significant differences in viewing time in six out of the eleven meta-analyses (reported in seven studies).
^
20
^

### Aim

To determine the effectiveness of a multi-component modular intervention on screen-based sedentary time and non-screen-based sedentary time in school-going adolescents in an urban area of Mangalore.

### Objectives

1.To measure the screen sedentary time and non-screen sedentary time among the adolescent population.2.To develop and implement a multicomponent modular intervention to reduce screen sedentary time and non-screen sedentary time among the adolescent population.3.To determine the effectiveness of the multi-component modular intervention on screen-based and non-screen-based sedentary time among adolescents.

## Methods

### Study area

Mangalore is a major port city and the commercial headquarters of the district of Dakshina Kannada in the south Indian state of Karnataka. In comparison to the national average of 85%, the district has a high literacy rate of 93.4%.
^
25
^ Mangalore is a leading educational hub owing to the plethora of educational institutions offering high-quality education. This interventional study will be carried out in the schools located in the urban area of Mangalore.

### Study design

This will be a cluster randomized control trial. Consolidated Standards of Reporting Trials (CONSORT) will be used for reporting the trial.
^
26
^

The Standard Protocol Items: Recommendations for Interventional Trials (SPIRIT) Guidelines are used to report the study’s protocol. A completed SPIRIT checklist is one of the prerequisites of the reporting guidelines.
^
27
^

### Duration of the study

January 2023 - September 2024

### Sample size calculation

Assuming that the proposed intervention in this study will result in a reduction in the mean screen-based sedentary time by 0.9 hours (54 minutes) between intervention and the control groups, with 80% power and at a level of significance of 5%, the sample size was calculated to be 180 in each of the intervention and control arm. A design effect of 2 was assumed since this was a cluster randomized trial, and a sample size of 360 was determined for both the intervention and control groups. The final sample size was 400 in each arm, taking into account a maximum loss of 10% throughout the six-month follow-up period.

The sample size was calculated using the following
equation ((1):

$$N=\frac{2\left[Z_{1-\frac{a}{2}}+Z_{1-\beta }\right]\sigma 2}{d^{2}}$$
(1)

Where,

*Z*
_1-
*α*/2_ = 1.96, Standard normal value at 5% level of significance

*Z*
_1-
*β*
_ = 0.84, Standard normal value at 80% power

*σ* = standard deviation = 3.025 hours
^
15
^

*d* = clinically significant difference = 0.9 hours

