### Exclusion criteria

Students whose parents do not give consent for their ward to participate in the study, students who do not assent to participate in the study and students who are not present on the day of baseline evaluation will be excluded from the study.

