### Sampling technique

The study participants will be selected from the 8
^th^ standard of selected schools. In schools with multiple sections of the same class, a simple random sampling technique will be employed to select one section, assuming a batch size of 40 students in each section. If the batch selected after simple random sampling has less than 40 students, the next batch will be selected by simple random sampling without replacement method, to reach the desired sample of 40 from the clusters.

The selected schools in the intervention arm would receive the comprehensive multicomponent modular intervention and the control group would not receive any intervention from the investigator. The students in the control group will undergo routine physical health education as per the school curriculum. They will be offered the comprehensive modular intervention only after the end of the final data collection.

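### The stated 80% power is about 76% to 78% once the 20 randomised schools are reckoned with, and the top-up rule leaves no margin for refusals or absence at the expected section size

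*Protocol article*

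**What the plan says.** All references are to the Methods of the protocol article.

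- **Sample size calculation.** The size comes from a two-sample formula for means with "1.96, Standard normal value at 5% level of significance" and "0.84, Standard normal value at 80% power", "standard deviation = 3.025 hours" and "clinically significant difference = 0.9 hours". The result is given as "with 80% power and at a level of significance of 5%, the sample size was calculated to be 180" per arm. An assumed design effect of 2 makes this 360. Then: "The final sample size was 400 in each arm, taking into account a maximum loss of 10% throughout the six-month follow-up period". No ICC is given.
- **Randomization technique.** Ten schools are allocated to each arm, 20 in all.
- **Sampling technique** and **Intervention procedure.** One section per school is taken, with 40 pupils expected. A further section is drawn on this condition: "If the batch selected after simple random sampling has less than 40 students, the next batch will be selected".
- **Exclusion criteria.** Pupils without parental consent or their own assent are left out, and "students who are not present on the day of baseline evaluation will be excluded from the study".
- **Study participants.** Little or no loss to follow-up is expected in class 8.

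**The concern.** A design effect enlarges the variance to allow for clustering. It does not change the reference distribution. With 10 schools per arm, a test that respects the unit of randomisation uses a t distribution with 2 × (10 − 1) = 18 degrees of freedom, critical value 2.10 rather than 1.96. A calculation built on 1.96 and 0.84 therefore overstates power when clusters are few.

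The second part concerns reaching 400 per arm. The only allowance in the sample size is for loss during follow-up. Refusals and baseline absences come earlier, and the rule for adding a section responds to how many pupils are in it, not to how many enrol.

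At stake is the trial's stated sensitivity. Readers would take it as having 80% power for 0.9 h when a valid unadjusted analysis of the planned sample has somewhat less, with more to lose if enrolment falls short.

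**Working it through.** **1. Reproduce the plan's figure.** Inputs from Sample size calculation: z values 1.96 and 0.84, SD 3.025 h, difference 0.9 h.

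- n per arm = 2 × (1.96 + 0.84)² × 3.025² / 0.9² = 2 × 7.84 × 9.1506 / 0.81 = 177.1. The plan states 180, which is within rounding.
- 180 × 2 = 360, and 360 / 0.9 = 400. Both are exact.

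**2. ICC implied by a design effect of 2.** Design effect = 1 + (m − 1) × ICC, with m pupils per school.

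- If it applies at m = 40 (the enrolment target): ICC = 1/39 = 0.026.
- If it applies at m = 36 (40 less 10% loss): ICC = 1/35 = 0.029.

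**3. Power with 18 degrees of freedom.** Effective n per arm = 10m / design effect. Standard error (SE) = 3.025 × √(2 / effective n). Noncentrality = 0.9 / SE. Power comes from the noncentral t with 18 df and two-sided critical value 2.101.

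| Case | Effective n per arm | SE (h) | Noncentrality | Normal power | t(18) power |
|---|---|---|---|---|---|
| 360 analysed, design effect 2 at 36 per school | 180 | 0.3189 | 2.82 | 80.6% | 76.1% |
| 360 analysed, design effect 2 at 40 per school (1.897 at 36) | 189.7 | 0.3106 | 2.90 | 82.6% | 78.2% |
| 400 analysed, design effect 2 at 40 per school | 200 | 0.3025 | 2.98 | 84.5% | 80.3% |

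In the first case the difference detectable at 80% power is about 0.945 h, against the planned 0.90 h.

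**4. Recruitment margin.** 10 schools × 40 pupils = 400 per arm, with no surplus. A section of exactly 40 never triggers the top-up, however many of its pupils refuse or are absent at baseline.

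**5. Sensitivity, on assumed inputs only.** The article gives neither an uptake rate nor an ICC. With 18 df, 10% loss and the ICC held at 0.029 to 0.026:

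- Uptake 90% (324 analysed per arm): 74% to 76%.
- Uptake 80% (288 analysed per arm): 71% to 73%.

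With full uptake, 360 analysed and an assumed ICC of 0.05, the design effect is 1 + 35 × 0.05 = 2.75 and power is about 62%. With an assumed ICC of 0.02 it is 1.70 and power is 82.5%.

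**6. What baseline adjustment could recover.** Adjusting for baseline screen-based sedentary time (SST) with correlation r multiplies the residual SD by √(1 − r²). Taking the first case in step 3, the same design effect and 17 df, power reaches 80% at r of about 0.32 and is about 87% at an assumed r = 0.5.

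**The case against.** **The arithmetic is right.** This stands in full. The chain 177 to 180 to 360 to 400 reproduces. What is at issue is the power claimed for it, not the number of pupils.

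**The shortfall is small and depends on the reading.** This largely stands. The 10% is given as a maximum, little loss is expected, and the only cluster size in the article is 40. If all 400 are enrolled and analysed, 80.3% is reached. But the plan sizes for 10% loss, and at that loss both readings of the design effect fall below 80%.

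**The 18-df test is not the one in the Data analysis section.** True. That section names individual-level tests, which raises a separate question about clustering. Tests that ignore clustering cannot support the 80%.

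**Baseline adjustment would make up the gap.** It probably could, since baseline SST is collected in both arms. The article does not name such an adjustment, and the power calculation takes no credit for it, so the figure here is for an unadjusted comparison.

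**Enrolment may not fall short.** Sections larger than 40, or small sections combined, could leave a surplus. The stated aim of the top-up is 40 pupils per school. A reader might infer that 400 is reachable only with complete consent and attendance. That holds only if every section has exactly 40, which the article assumes rather than fixes. What remains is that no wording triggers a replacement for refusals or absence.

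**The equation as it appears lacks the square on the bracket.** A reader might infer that the sample size is wrong, because that form gives about 63. The stated 180 can only have come from the squared form, and the superscript on sigma is also lost in the text as read, so an extraction artefact is plausible. It is no ground for this point.

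**Conclusion.** The point holds, at modest size. At the plan's own inputs (10 schools per arm, 360 analysed per arm, SD 3.025 h, design effect 2), unadjusted power for 0.9 h is about 76% to 78%. The range reflects whether the design effect applies at 36 or at 40 pupils per school. The cost in detectable difference is at most about 0.045 h, or 2.7 minutes a day.

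This rests on a cluster-level comparison with 18 df, equal numbers per school and no baseline adjustment.

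A reader might infer that true power is nearer 71% or 62%. The article does not support that. Those figures need an assumed uptake of 80% or an assumed ICC of 0.05, and an ICC of 0.02 would put power above 80%. They show only how far the claim depends on a design effect offered without a stated ICC.

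The enrolment rule is a lesser, practical weakness: at the expected section size there is no margin for pupils lost before baseline.

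**What to change.** 1. **Restate the power.** Say that with 10 schools per arm, 18 df and 360 analysed per arm, unadjusted power for 0.9 h is about 76% to 78%, and that the difference detectable at 80% is up to about 0.945 h.
2. **State the ICC.** Give the value implied by the design effect (0.026 to 0.029), the cluster size it refers to and its support, with a sensitivity value such as 0.05.
3. **Optionally, state what baseline adjustment recovers.** If adjustment for baseline SST is planned, give the assumed correlation and the resulting power.
4. **Change the top-up trigger.** Draw a further section when fewer than 40 pupils in a school have consented, assented and are present at baseline.

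The cost is a less favourable stated power, a one-line change to the sampling rule, and some added fieldwork where a second section is needed. No school is added. The article says that recruitment has not started, so all of this can be done beforehand, with resubmission to the ethics committee where its own rule on protocol changes requires it.
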